### 3.2.3. **Antiviral Effects of Azithromycin Against COVID-19**

Azithromycin is a broad-spectrum azalide antibiotic used to treat a number of bacterial infections, including pneumonia. Azithromycin has shown antiviral activity *in vitro* against Zika, Ebola, rhinoviruses, and other respiratory viruses. Although the mechanism of its antiviral activity is not clear, some findings suggest it may be associated with augmentation of interferon response. Alternatively, azithromycin may convey antiviral activity by increasing the pH of cell organelles such as endosomes and the *trans*-Golgi network. Changing the pH of intracellular vesicles may alter the glycosylation of ACE2, a key receptor for cell entry for SARS-CoV-2. PK modelling supports the azithromycin regimen will include an additional loading dose on day 1 to allow earlier achievement of azithromycin concentrations in lung that consistently achieve the EC50 determined for SARS-CoV-2.

### 3.2.4. **Antiviral Effects of Lopinavir and Ritonavir Analogues Against COVID-19**

Lopinavir-ritonavir (LPV/r), is a combination medication that has been used to treat HIV/AIDS. Lopinavir is a HIV type 1 aspartate protease inhibitor that is usually “boosted” with ritonavir to increase the plasma half-life of lopinavir through the inhibition of cytochrome P450. Lopinavir has been shown to have in-vitro inhibitory activity against SARS-CoV [Error! Reference source not found., Error! Reference source not found., Error! Reference source not found.]. Compared to ribavirin as a historical control group, it has been previously shown that lopinavir–ritonavir (400 mg and 100 mg, respectively) can reduce the risks of adverse clinical outcomes such as acute respiratory distress syndrome and death as well as viral load among patients with SARS. [Error! Reference source not found., Error! Reference source not found., Error! Reference source not found.] Based on *in vitro* testing and previous clinical evaluation, LPV/r is an important treatment regimen that should be tested for SARS-CoV-2. Although a recent open-label clinical trial did not show efficacy of LPV/r to decrease days of hospitalization or viral shedding, this trial focused on patients who were already hospitalized, likely due to LRTI and used a suboptimal dosing strategy. The proposed trial will treat participants earlier in the illness, and supported by PK modelling, will use a higher loading doses on day 1, which will allow earlier achievement of LPV concentrations exceeding SARS-CoV-2 EC50 values in the lung.

### 3.2.5. **Rationale for Ascorbic Acid Control as a Comparator**

In healthy adults, COVID-19 disease is likely to present as an upper respiratory viral infection, characterized by a febrile disease with cough and fatigue. Symptom reporting may vary based on participants’ perception as to whether they are taking investigational antivirals or ascorbic acid, but the primary study endpoints of LRTI and viral shedding are not affected. There is no rigorously-proven therapy for individuals with outpatient COVID-19 disease, although multiple therapies are under investigation.

Because there is not established therapy, use of a control is acceptable and ethical both for participants’ health and safety as well as ensuring the most rigorous trial design to evaluate an intervention for COVID-19 disease caused by SARS-CoV-2. As there are multiple intervention regimens with different dosing schedule and route, full blinding for patients and clinicians will not be feasible. Participants will be blinded to their allocation to the extent possible.

The dose of ascorbic acid chosen for this protocol is considered to be safe and well tolerated. All participants, regardless of assigned group, will be able to take additional ascorbic acid (e.g., over the counter vitamins, or through food) should they choose, as there is no known maximum daily safe dose of ascorbic acid. Clinical trial evidence has demonstrated that ascorbic acid, alone or in combination with other micronutrients, does not substantially reduce the risk of upper respiratory infections or severe consequences of infectious processes; thus, ascorbic acid is not expected to have a prevention effect for SARS-CoV-19 and is considered a placebo-equivalent product for this study.

### 3.2.6. **Rationale for Dosing Selection of Experimental Interventions**

As the COVID-19 epidemic remains very fluid and new data are emerging from observational and clinical trials daily, this protocol is written to allow adaptation to incorporate additional medications throughout the trial. The rationale for dosing selection of each experimental interventions will be provided in each of the corresponding appendix. This modular structure of protocol is used for this platform trial that may end up adding new experimental interventions during the trial.

### 3.3. **Benefit/Risk Assessment**

**There is equipoise as to whether the *in vitro* efficacy of any drug will translate into efficacy to prevent LRTI.** COVID-19 disease can be unpredictable in its severity, but a 3.4% mortality rate has been observed among clinical pneumonia cases. The elderly (>60 years) and those with medical comorbidities are at highest risk of poor outcomes. Moreover, transmission in younger persons amplifies infection in communities, putting susceptible persons at risk. There is no proven drug for treatment of those with COVID-19 disease.

**QT prolongation:** Azithromycin and LPV/r are widely used throughout Brazil without the requirement of QT measurements prior to initiation. LPV/r has been reviewed by CredibleMeds (crediblemeds.org) but the evidence available at this time did not result in a decision for it to be placed as a risk medicine for QT prolongation and Torsades de Pointes. Azithromycin has been associated with QT prolongation. However we will exclude patients with a baseline QTc interval of > 470 ms in males, and > 480 ms in females.

**LPVr use in undiagnosed HIV-positive patients:** Ten days of LPV/r monotherapy is unlikely to cause resistance (high barrier to resistance) and is effective for viral suppression. The risk of HIV-associated immune reconstitution inflammatory syndrome (IRIS) is possible, and the time of onset varies from days to months after antiretroviral initiation. Ten days of LPV/r potentially carries a low risk of unmasking IRIS in undiagnosed HIV-positive patients. Should IRIS occur, it will be recorded as a serious adverse event (SAE). Testing for HIV prior to enrolment is not pragmatic as it exposes health care workers to SARS-CoV-2 infection and there is no referral pathway for newly diagnosed HIV-positive patients with SARS-CoV-2 co-infection. In this study we minimise interaction between study staff and patients using Telehealth.

**Drug interactions between study arms and rifampicin-treated and ART treated patients:** We included an explicit exclusion criteria to exclude patients with potentially clinically significant pharmacokinetic and pharmacodynamic drug interactions as determined by the study clinical pharmacologist. As far as possible, we want to study HIV-positive and patients treated for pulmonary tuberculosis as they are potentially a high risk for severe disease who could benefit from an early treatment. If one of the study experimental drugs are considered to put the patient at increased risk due to drug interactions, randomization for such patients will be limited to the study arms that are deemed to be safe by the study clinical pharmacologist.

**Misclassification as low-risk:** We thoroughly question participants about their medical history to best as possible correctly classify them as high- or low-risk for co-morbidities. We will also request participants for consent to access their medical records to review for co-morbidities.

#### 4. Objectives and Endpoints

##### 4.1. Objectives and Endpoints for Brazil

| Brazil                                                                                                                                                                                                                                                                                                           |                                                                                                                                                                                                                                                                                                                                                                                       |
|------------------------------------------------------------------------------------------------------------------------------------------------------------------------------------------------------------------------------------------------------------------------------------------------------------------|---------------------------------------------------------------------------------------------------------------------------------------------------------------------------------------------------------------------------------------------------------------------------------------------------------------------------------------------------------------------------------------|
| Objectives                                                                                                                                                                                                                                                                                                       | Endpoints                                                                                                                                                                                                                                                                                                                                                                             |

| 
 
To test the efficacy of experimental interventions to prevent progression to LRTI, among persons with SARS-CoV-2 infection who are at high risk of progression
 
To test the efficacy of experimental interventions to reduce SARS-CoV-2 viral shedding
 
 | 
 
LRTI, defined by SpO2<93% or decline from baseline of 6% in 2 measurements at least 2 hours apart. Initially, the trial is statistically powered for this endpoint in high-risk population.
 
Proportion of persons with clearance of SARS-CoV-2 from nasal swabs or saliva, defined as 1 negative swab
 
 |
| 
 
To test the safety and adherence of experimental interventions for treatment of high-risk outpatients with SARS-CoV-2 infection
 
                                                                                                                                | 
 
Serious adverse events (including death, hospitalization) and adverse events resulting in treatment discontinuation up to 28 days
 
Proportion of non-adherent patients with interventions
 
                                                                                                                                   |
| 
 
To test whether any of the experimental interventions has an effect on hospitalization and mortality among persons who become hospitalized with COVID-19 disease (continued from primary outcome)
 
                                                              | 
 
Proportion hospitalized for COVID-19 progression
 
Days of hospitalization
 
Mortality for any causes after randomization up to 90 days
 
Mortality due to pulmonary complications
 
Mortality due to cardiovascular complications
 
                                                                      |
| Date/version: May 19, 2020 – V1.0                                                                                                                                                                                                                                                                         | Page: 21                                                                                                                                                                                                                                                                                                                                                                       |

|                                                                                                                                                                                                                                        |                                                                                                                                                                                                                                                                                                                                                                                                                                                                                                                                                                                                                                                                                                                                                            |
|----------------------------------------------------------------------------------------------------------------------------------------------------------------------------------------------------------------------------------------|------------------------------------------------------------------------------------------------------------------------------------------------------------------------------------------------------------------------------------------------------------------------------------------------------------------------------------------------------------------------------------------------------------------------------------------------------------------------------------------------------------------------------------------------------------------------------------------------------------------------------------------------------------------------------------------------------------------------------------------------------------|
| 
 
To test whether any of the experimental interventions decrease resolution rate for symptomatic SARS-CoV-2 infection / COVID-19 disease
 
                                               | 
 
Proportion of days with fever after randomization
 
Proportion of days with respiratory symptoms after randomization
 
Time until clinical improvement (up to 28 days), defined normalization of temperature, respiratory rate, SaO2, and cough relief (> 50 in relation to baseline measured on a visual analog scale) in the last 72 hours;
 
Reduction in the perception of dyspnea (upper respiratory tract respiratory symptoms scale - WURSS-11) on days 0, 3, 7, 14 and 28 days;
 
Time to clinical failure, defined as time to need for hospitalization due to dyspnea, death, need for mechanical ventilation, shock with need for vasoactive amines;
 
 |
| 
 
To test whether any of the experimental interventions is associated with decreased viral shedding from self-collected nasal swabs over 14 days: Day 1, Day 10 and Day 14 (+/-1 days)
 
 | 
 
Proportion of days with SARS-CoV-2 detected from mid-nasal swabs by PCR
 
Change in viral load on day 10 and day 14 after randomization from baseline
 
                                                                                                                                                                                                                                                                                                                                                                                                                                                                                                                                             |
| 
 
To test the quality-of-life (QoL) of experimental interventions for treatment of high-risk outpatients with SARS-CoV-2 infection
 
                                                     | 
 
Change in quality of life measured by Eq-5D-5L from baseline
 
                                                                                                                                                                                                                                                                                                                                                                                                                                                                                                                                                                                                                                             |

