| 
 
To test whether any of the experimental interventions decrease resolution rate for symptomatic SARS-CoV-2 infection / COVID-19 disease
 
                                                            | 
 
Proportion of days with fever after randomization
 
Proportion of days with respiratory symptoms after randomization
 
Time until clinical improvement (up to 28 days), defined normalization of temperature, respiratory rate, SaO2, and cough relief (> 50 in relation to baseline measured on a visual analog scale) in the last 72 hours;
 
Reduction in the perception of dyspnea (upper respiratory tract respiratory symptoms scale - WURSS-11) on days 0, 3, 7, 14 and 28 days;
 
Time to clinical failure, defined as time to need for hospitalization due to dyspnea, death, need for mechanical ventilation, shock with need for vasoactive amines;
 
 |
| 
 
To test whether any of the experimental interventions is associated with decreased viral shedding from self-collected nasal swabs over 14 days: Day 1, Day 10 and Day 14 (+/-1 days)
 
              | 
 
Proportion of days with SARS-CoV-2 detected from mid-nasal swabs by PCR
 
Median quantity of SARS-CoV-2 detected from mid-nasal swabs by PCR
 
Change in viral load on day 10 and day 14 after randomization from baseline
 
                                                                                                                                                                                                                                                                                                                                                                                                                                                                 |

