## 2. Schedule of Activities

### 2.1. Schedule of activities for Brazil

| FLOWCHART                                                                                    | STUDY VISIT SCHEDULE                             |                                                     |                               |                              |                               |                              |                               |                               |                               |                               |                                                        |
|----------------------------------------------------------------------------------------------|--------------------------------------------------|-----------------------------------------------------|-------------------------------|------------------------------|-------------------------------|------------------------------|-------------------------------|-------------------------------|-------------------------------|-------------------------------|--------------------------------------------------------|
|                                                                                              | Screening and treatment period                   |                                                     |                               |                              |                               |                              | Post-treatment period         |                               |                               |                               |                                                        |
|                                                                                              | Screening 
Visit
(D-minus 1) | Baseline and
randomization
 D-0 | D1-2 
+1 day | D-3 
+1 day | D4-8 
+1 day | D-9 
±1 day | D-10 
±1 day | D-14 
±1 day | D-28 
±2 day | D-56 
±5 day | D-90 or Early
Termination
 ±5 days |

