| Adverse Events (AEs)                                                                         |                                                  | X                                     | X                             | X                            | X                             | X                            | X                             | X                             | X                             |                               |                                                        |
| Dyspnea Scale (WURSS-11)                                                                     |                                                  | X                                     | X                             | X              | X               | X              | X               | X               |                               |                               |                                                        |
| Tisdale scale                                                                                |                                                  | X                                                   |                               |                              |                               |                              |                               |                               |                               |                               |                                                        |
| EQ-5D-5L                                                                                     |                                                  | X                                     |                               |                              |                               |                              |                               |                               | X               |                               | X                                        |

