#### **10.1.2. Day 1 Through Day 14**

The participant will do the following every day from Day 2 through Day 14 (unless stated otherwise), inclusive:

- Take study therapy (for a total treatment of 10 days of treatment)
- Tolerance towards the assigned therapy
- Confirmation of adherence to study therapy dosing (Day 10)
- Daily dosing time from the day prior
- Reporting of adverse events
- Cardiac measurement using Kardiamobile monitors (Day 3, Day 7, Day 10, and Day 14)
- Pulseoximeter measurements (Day 3, Day 7, Day 10, and Day 14)

| Harmonized protocol document                                                          |
|---------------------------------------------------------------------------------------|
| Short title: Outpatient Management of SARS-CoV-2 for High-Risk Adults in LMICs |

- Measurement of heart rate (pulse oximeter) at rest after the participant remained seated at rest for 5 minutes
- Review of clinical symptoms and hospitalization
- WURSS-11 survey for dyspnea

A study team member will be available via Telehealth, text messaging, or telephone to provide support for completion of study procedures. Participants will be clinically assessed for signs and symptoms of respiratory distress and will have in person assessment of AEs. As needed, additional contact with the study clinician or staff will be conducted at the request of the participant (e.g., if developing concerning symptoms or an adverse event) or if needed to clarify study procedures or follow-up symptoms.

The health care provider will make home-visits to collect nasal-swabs or saliva samples for RT-PCR on Day 3, Day 7, Day 10, and Day 14. These samples collected on Day 14 will be used to analyse the viral shedding related outcomes. Other samples collected on Day 3, Day 7 and Day 10 will be stored for a biobanking deposit.

A study team member will be available via Telehealth, text messaging, or telephone to provide support for completion of study procedures.

Clinical outcomes will be confirmed through the electronic health record, if possible.

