#### **10.1.3. Day 28 (+/- 5 days)**

Participants will be followed-up via Telehealth, text messaging, or telephone:

- EQ-5D-5L
- Review of AEs, clinical symptoms, and hospitalization

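### The WURSS-11 dyspnea endpoint runs to Day 28, but no WURSS-11 is scheduled after Day 14

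*Protocol*

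**What the plan says.** Section 4.1 lists, among the secondary endpoints on symptom resolution, "Reduction in the perception of dyspnea (upper respiratory tract respiratory symptoms scale - WURSS-11) on days 0, 3, 7, 14 and 28 days". The Synopsis table carries the same endpoint with the same days: "WURSS-11) on days 0, 3, 7, 14 and 28 days".

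Data collection is set out in three places:

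- **Section 2.1, Schedule of Activities.** The row "Dyspnea Scale (WURSS-11") is marked at D0, D1-2, D3, D4-8, D9, D10 and D14. It is blank at D28, D56 and D90.
- **Section 10.1.2.** The list containing "WURSS-11 survey for dyspnea" is introduced by "The participant will do the following every day from Day 2 through Day 14 (unless stated otherwise), inclusive".
- **Section 10.1.3, Day 28.** Two items are listed: EQ-5D-5L and "Review of AEs, clinical symptoms, and hospitalization". Section 10.1.10 describes the same time point again, only as a contact about general well-being.

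Sections 9 and 11 state that the timing of procedures is summarized in the schedule, and that keeping to the study design requirements, including those in the schedule, is essential.

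**The concern.** The endpoint definition asks for a score that no operational section tells anyone to collect. If sites work to the schedule and the Day 28 contact list, the trial reaches its analysis with the last time point of a stated secondary endpoint absent in all arms.

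This is not the usual missing-data problem. Values missing for some participants can be modelled or imputed from those who have them. A time point absent by design for everyone offers no observed values to work from, so the statistical analysis plan cannot repair it.

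Day 28 is also the only WURSS-11 time point well clear of treatment. Treatment lasts 10 days, so Day 14 falls only four to five days after it ends, depending on whether the last dose is counted on Day 10 or Day 9. Without Day 28 the endpoint says little about how dyspnea evolves after treatment, and the trial would have to report an endpoint that departs from its own definition.

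**Working it through.** The protocol gives no figure to reproduce here. The check compares the days in the endpoint with the days on which the instrument is collected.

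**Step 1. Endpoint days against collection.**

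| Endpoint day | Schedule, Section 2.1 | Encounter text |
|---|---|---|
| 0 | marked (D0) | listed in Section 10.1.1 |
| 3 | marked (D3) | listed in Section 10.1.2 |
| 7 | marked (within D4-8) | listed in Section 10.1.2 |
| 14 | marked (D14) | listed in Section 10.1.2 |
| 28 | blank | not listed in Section 10.1.3 or 10.1.10 |

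Four of the five named days are covered; Day 28 is not.

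**Step 2. Is the blank cell only a shifted column?** The adverse-event row of the same table has eight marks, D0 to D28, one more than the WURSS-11 row. The EQ-5D-5L row is marked at D0, D28 and D90. Both agree with the Day 28 text in Section 10.1.3, which lists EQ-5D-5L and adverse events. The columns are therefore aligned. The blank WURSS-11 cell at D28 agrees with the same text.

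**Step 3. Does another passage supply the score?**

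- Section 3 says participants complete surveys on Days 28, 56 and 90 but names no instrument.
- Section 11.1.3 names the WURSS-11 as a patient-reported outcome but gives it no Day 28 time point.
- The review of clinical symptoms at Day 28 is not the WURSS-11. Section 10.1.2 lists a symptom review and the WURSS-11 as separate items.

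**Step 4. Size.**

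- Post-baseline time points in the endpoint: Days 3, 7, 14 and 28. Unscheduled share: 1 / 4 = 25%. This counts time points; it is not a share of statistical information.
- Scores not scheduled, three arms of 492 (Section 5.1): 3 × 492 = 1,476.
- Scores not scheduled, three arms at the initial target of 165 (Section 5.2): 3 × 165 = 495.
- Illustration with the drop-out rates tabulated in Section 12.1: 1,476 × 0.95 ≈ 1,402 at 5%, and 1,476 × 0.80 ≈ 1,181 at 20%.

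The possible fourth arm in Section 5.1.1 is left out of these counts.

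**The case against.** The strongest reply is that the score is unscheduled rather than certain to be missing. The schedule only summarizes procedures. The adherence rule covers the study design requirements as a whole, and nothing says that the schedule overrides Section 4.1. The Introduction also foresees surveys at Day 28. A site could read these together and give the WURSS-11. That stands as a matter of wording: the score will be absent if sites follow the detailed instructions, not absent with certainty. It does not remove the contradiction. The only questionnaire the protocol names for Day 28 is the EQ-5D-5L, and collection on a site's own initiative would be uneven.

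The second reply is that little depends on it. This is one of many secondary endpoints, and change from baseline can be computed at Days 3, 7 and 14. No primary endpoint, power calculation or safety conclusion rests on the Day 28 score. That stands in full and sets the severity.

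The third is that 1,476 is too precise. That also stands: it is an upper limit for three arms of 492 without deaths or losses, and the range belongs beside it. The 25% does not depend on the sample size.

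**Conclusion.** The protocol contradicts itself. The endpoint is stated twice with a Day 28 assessment, while the schedule and both descriptions of the Day 28 contact omit the instrument. Followed as written, the WURSS-11 endpoint lacks its final time point: one of four post-baseline assessments for every participant, at most 1,476 scores at 492 per arm or 495 at 165 per arm. This assumes that sites work to the schedule and the visit lists, and that the unnamed Day 28 surveys in the Introduction do not include the WURSS-11.

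The point is minor. It affects one secondary endpoint at one time point, and the scores at Days 0, 3, 7 and 14 remain available. It is worth settling before participants pass Day 28, because a score missed at that contact cannot be collected later.

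**What to change.** Choose one of two changes.

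1. **Keep Day 28.** Mark the WURSS-11 in the D28 column of Section 2.1 and add it to Section 10.1.3, alongside the EQ-5D-5L at the existing remote contact. Bring the general Day 28 descriptions in Sections 8.1.5 and 10.1.10 into line. The Day 28 window must be reconciled at the same time: it is ±2 days in the schedule and ±5 days in Section 10.1.3, so the timing of the added score would otherwise be unclear.
2. **End the endpoint at Day 14.** Delete Day 28 from the WURSS-11 endpoint in the Synopsis and in Section 4.1.

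The first adds one short questionnaire to a contact that already takes place. The second changes wording only. Either is a protocol amendment, and the new Section 7.10 text in the amendment summary says amendments need regulatory and ethical approval before implementation. It is sensible to combine the change with another amendment, if one is due in time.
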